### Participant recruitment

The Hepatology Outpatient Centre’s appointment database will be prescreened for eligible participants who are scheduled for routine review by a hepatologist. Persons identified as eligible will be contacted via telephone in the week preceding their appointment to discuss the study and offer participation. Participants will be given instructions to arrive 15 minutes early for their appointment, bring all medications to the clinic, and ask their carer or responsible family member to accompany them if appropriate. Consented participants will be randomly allocated to one of the two study arms: (1) intervention or (2) usual care.

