### Primary outcome

#### Medication discrepancies

Discrepancies between patient-reported and clinician-documented current medications will be obtained via the patient questionnaire (medication recall), patient interview (reconciliation for intervention participants only), and medical record review (clinician documentation). The clinical significance of discrepancies will be determined by blinded comparison at the completion of the study using a risk matrix tool (Fig. 2), which assigns a composite ranking of severity, likelihood, and duration, as described in the Methods subsection “Medication-related problems” above. Discrepancies (between medications, doses, and frequency of administration) will be examined at baseline and follow-up (*t*
_3_) for both groups. A composite endpoint of frequency (counts of) and potential risk will be examined by measuring total frequency of high/very high risk discrepancy occurrence and the frequency of high/very high risk discrepancy occurrence per patient.

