### Data analysis

Data will be coded and stored in a password-protected database and analyzed using a statistical software package (IBM SPSS Statistics version 20.0; IBM, Armonk, NY, USA). Study endpoints experienced for each treatment group will be formally analyzed on an intention-to-treat basis [36]. Important potential confounders will be included in a secondary multivariate analysis (e.g., hospital admission, mortality). Post hoc subgroup analysis will be used to further explore outcomes according to the intensity of the intervention and completeness of relevant personalized education received by intervention participants.

The study endpoints will be presented quantitatively (proportions, statistical differences between groups) and qualitatively (description of discrepancies, MRPs, and some patient-reported medication beliefs and illness perceptions). All tests will be two-tailed, and significance will be set at α = 0.05. Continuous and normally-distributed variables will be presented as mean ± SD. Differences between groups will be analyzed using one-way analysis of variance. Non-normally distributed data will be presented as median (range), and nonparametric tests will be used to analyze differences between groups. Categorical data will be analyzed using Pearson’s chi-square test or Fisher’s exact test. Pearson’s correlation or Spearman’s rank correlation coefficient will be used to identify linear relationships between normally distributed and non-normally distributed continuous variables, respectively.

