Differences in the study endpoints of interest will be examined between the intervention and control groups at baseline and at follow-up. The endpoints will be examined at baseline to test for homogeneity between groups (effectiveness of randomization) and to identify clinical variables that may influence endpoints (e.g., Model for End-Stage Liver Disease score; Child-Turcotte-Pugh classification; decompensation history, including event date, type, severity, and recurrence; hospitalization frequency; age; sex; biochemical abnormalities; and other prognostic variables). Clinically significant differences at baseline between groups will be adjusted for during the final analysis. Changes in the frequency of medication discrepancies, self-reported adherence, QoL, medication beliefs, illness perceptions, and patient knowledge at follow-up will be examined to measure the effect of the intervention on study outcomes at group and individual levels. The primary endpoint of medication discrepancies will be explored using total frequency of instances and frequency of instances per patient and per medication group. Comparison between intervention and control groups at baseline and *t*
_3_ will be made using total number of instances per group, total number of high/very high risk instances per group, mean/median number of instances per patient, and mean/median number of high/very high risk instances per patient.

Predictors of clinical outcomes will be identified using binary logistic regression to determine the OR (95% CI). A multivariable logistic regression model will be used to determine independent predictors for patient outcomes. The multivariable logistic regression model will be constructed using variables of clinical significance (severity of disease; decompensation history, including date, type, severity, and frequency of events; other prognostic variables) and statistical significance as determined by univariate analysis.

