### Power calculation and sample size determination

On the basis of a primary endpoint of a 50% reduction in medication discrepancies (3.12 ± 2.5 per patient [6] to 1.56 per patient), 41 participants will be required per treatment arm to achieve ≥80% statistical power. Median survival in decompensated cirrhosis is 2 years [37]. Therefore, a 6-month mortality rate between 10% and 15% among the study cohort is predicted. The Hepatology Outpatient Centre’s attendance failure/reschedule rate is approximately 20%. Therefore, a possible 30% loss will be accounted for, and at least 106 participants will be recruited.

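### The primary endpoint is described inconsistently: the stated power covers only all discrepancies per patient, and none of the four listed comparisons is named as deciding

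*Protocol article*

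**What the plan says.** The protocol article describes the primary endpoint in five places, and the descriptions differ.

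- **Study aims and hypotheses:** the primary aim covers both how many discrepancies occur and how severe they are.
- **Hypotheses, H1:** fewer discrepancies, with no restriction by risk.
- **Primary outcome, Medication discrepancies:** discrepancies in general are examined at baseline and t3 in both groups. The section then gives a composite of frequency and risk, obtained by "measuring total frequency of high/very high risk discrepancy occurrence and the frequency of high/very high risk discrepancy occurrence per patient".
- **Power calculation and sample size determination:** the sizing rests on "a primary endpoint of a 50% reduction in medication discrepancies (3.12 ± 2.5 per patient [6] to 1.56 per patient", which counts discrepancies of every risk level. It concludes that "41 participants will be required per treatment arm to achieve ≥80% statistical power".
- **Data analysis:** the primary endpoint is called medication discrepancies without restriction. The arms are then compared at baseline and t3 "using total number of instances per group, total number of high/very high risk instances per group, mean/median number of instances per patient", with the per-patient high/very high risk number as a fourth measure.

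The significance rule is general: "All tests will be two-tailed, and significance will be set at α = 0.05".

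**The concern.** Two classes of discrepancy (all, and high/very high risk), each summarised two ways (group total and per patient), give four candidate primary results. The text does not say which one decides the trial. Three consequences follow.

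1. The power statement belongs to one of the four. A reader who takes the composite under Primary outcome as the endpoint would attach 80% power to a measure for which the document gives no mean, SD or share.
2. If the deciding result can be picked once the data are known, the chance of a false positive claim exceeds 5%, although each test is run at 0.05.
3. Patients are randomised, not discrepancies. A raw group total ignores the grouping of discrepancies within patients. It also rises and falls with the number of patients per arm who reach t3, and the protocol expects about 30% loss before then.

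**Working it through.** **Inputs from the document.** Mean 3.12 falling to 1.56 per patient, SD 2.5, 41 per arm, power of at least 80% (Power calculation); two-sided α = 0.05 (Data analysis). Equal allocation is implied by the 41 per arm.

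**Step 1. Reproduce the stated size.** n per arm = 2 × [SD × (z₀.₉₇₅ + z₀.₈₀) / difference]² = 2 × [2.5 × (1.960 + 0.842) / 1.56]² = 40.3, rounded up to 41. Power at 41 = Φ(1.56 / (2.5 × √(2/41)) − 1.96) = 0.807 (0.797 by noncentral t). The figure is sound for all discrepancies per patient.

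**Step 2. Power for high/very high risk discrepancies per patient.** The share f is not given, so a range is assumed, with a 50% reduction also assumed. A negative binomial matched to mean 3.12 and variance 2.5² = 6.25 has dispersion (6.25 − 3.12) / 3.12² = 0.32. With share f, the control mean is m = 3.12f, the control variance is v₀ = m + 0.32m², and the difference to detect is m/2. The intervention-arm variance v₁ uses m/2 in place of m.

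- Common SD: power = Φ((m/2) / √(2v₀/41) − 1.96).
- Arm-specific variances: power = Φ((m/2) / √((v₀ + v₁)/41) − 1.96).

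| Assumed share f | Control mean | Control SD | Power, common SD | Power, arm-specific | n per arm for 80%, common SD |
|---|---|---|---|---|---|
| 0.1 | 0.31 | 0.59 | 23% | 29% | 222 |
| 0.2 | 0.62 | 0.87 | 37% | 48% | 121 |
| 0.3 | 0.94 | 1.10 | 48% | 62% | 88 |
| 0.5 | 1.56 | 1.53 | 64% | 78% | 61 |
| 0.75 | 2.34 | 2.02 | 74% | 88% | 48 |
| 1 | 3.12 | 2.50 | 81% | 93% | 41 |

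Simulated t-tests on these counts gave 47% at f = 0.2 and 79% at f = 0.5, in line with the arm-specific column. The common-SD column is the convention that reproduces the protocol's own 41.

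**Step 3. Overall error if any comparison may count.** Null trials were simulated 20,000 times at 41 per arm, with f = 0.2, 0.3 and 0.5.

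- Each per-patient t-test alone: about 5%.
- Either of the two per-patient tests: about 7–9%. Independent tests would give 1 − 0.95² = 9.75%; the correlation lowers it.
- Group total of all discrepancies tested as a simple Poisson count (assumed): variance/mean = 6.25/3.12 = 2.0, so the actual error is 2 × [1 − Φ(1.96/√2.0)] = about 17%.
- Any of the four, with totals tested that way: about 20%.

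**Step 4. Totals and completion.** With the same mean in both arms, each extra patient who reaches t3 adds 3.12 discrepancies on average to that arm's total. Unequal completion therefore produces a difference in totals without any treatment effect.

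**The case against.** The case against has four parts.

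- **All discrepancies dominate the text.** H1, the sizing and the opening of the endpoint sentence in Data analysis all point to all discrepancies, and Primary outcome also says discrepancies in general are examined. This stands. A reader might infer that the endpoint is defined only on high/very high risk discrepancies and sized on something else. The document does not support that; the fault is inconsistent description.
- **The stated power and alpha are not false.** This stands too. The power reproduces for the endpoint it was computed on, and 0.05 is set per test with no family-wise claim. It would be wrong to say that neither holds.
- **No test for totals is named.** The plan speaks of exploring and comparing, and does not say that totals receive p-values. The 17% and 20% figures therefore depend on an assumed Poisson or chi-square test. Nor are the comparisons four separate chances: for fixed arm sizes a total carries the same information as the per-patient mean, and high-risk counts are a subset of all counts. The per-patient tests in Data analysis use the observed variance or ranks, so overdispersion does not invalidate them.
- **Hierarchy and count model can be left to an SAP.** The absence of a multiplicity rule or a negative binomial model is indeed no finding here. What remains is that the article gives incompatible descriptions of its primary endpoint, and an SAP could settle this only by choosing one of them.

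The power loss is also conditional. With a share of 75% and arm-specific variances, power for the high-risk count would be 88%.

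**Conclusion.** The point holds as an inconsistency in the primary endpoint. The stated power of at least 80% at 41 per arm is correct for all discrepancies per patient and does not extend to the high/very high risk composite. For an assumed share of 20–50% and an assumed halving, power for that per-patient count is about 37–64% with a common SD, or about 47–80% with arm-specific variances.

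With no deciding comparison named, the overall error is about 7–9% if either per-patient test may count. The 20% figure applies only if totals are tested as simple counts and any of the four may count; the plan states neither. The inconsistency leaves the choice of deciding result open until after the data are seen, so it should be resolved before the arms are compared.

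**What to change.** Before any comparison by arm, amend the wording of Primary outcome, Data analysis and the aims so that they agree:

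1. Name one primary comparison: the number of all discrepancies per patient at t3, intervention against usual care. This matches the existing sample size.
2. Make the per-patient count of high/very high risk discrepancies the first secondary endpoint, either tested only if the primary is significant or labelled supportive. State that the 80% power figure does not apply to it. This keeps the severity part of the aim.
3. Report group totals descriptively, with the number of patients contributing in each arm and without p-values.
4. The per-patient tests already listed in Data analysis may stay. A count model that allows for overdispersion is optional.

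The cost is wording only. The drawback is that the high-risk count is no longer a separate route to a positive primary result. Keeping both per-patient counts as alternative primaries with a Bonferroni split would cost more: the all-discrepancy comparison alone would need 2 × [2.5 × (2.241 + 0.842) / 1.56]² = 48.8, or 49 per arm, and would have 72% power at 41. Trial status reports that recruitment is complete, so enlarging the trial is not a simple remedy.

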## Methods/design

### Study aims and hypotheses

The primary aim of the study is to determine whether the intervention (medication review, reconciliation, and additional education by a clinical pharmacist) reduces the frequency (counts) and severity (measure of clinical significance) of discrepancies between patient-reported and medical record-documented “current” medications. The secondary aims are to describe the impact of the intervention on medication adherence, quality of life (QoL), medication and illness beliefs, patient knowledge of disease and self-management tasks related to decompensation history and prescribed therapy, and the frequency of hospitalization for management of cirrhosis-related complications, non-cirrhosis-related complications, and survival. The sustainability of the intervention in the current health care system in relation to costs and cost-effectiveness will also be evaluated.

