#### Hypotheses

Compared with patients receiving usual care, patients who receive the tailored (additional) education and medication management intervention are hypothesized to benefit in the following ways:

(H1) Fewer medication discrepancies

(H2) Improved medication adherence

(H3) Improved QoL

(H4) Improved illness perceptions

(H5) Improved medication beliefs

(H6) Improved knowledge of disease self-management tasks related to prescribed medications

(H7) Fewer hospital admissions

(H8) Longer survival time

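### The protocol does not fix one primary measure of medication discrepancies, and the stated power of at least 80% applies only to the count of discrepancies of any risk level

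*Protocol article*

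**What the plan says.** Five places in the protocol article bear on what the primary measure is.

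- **Study aims and hypotheses.** The primary aim is to determine whether the intervention "reduces the frequency (counts) and severity (measure of clinical significance) of discrepancies". Frequency and severity stand together, with neither placed first.
- **Hypotheses.** H1 reads "Fewer medication discrepancies", with no restriction by risk.
- **Primary outcome, Medication discrepancies.** Discrepancies are examined at baseline and at t3 in both groups. The section then sets a composite of frequency and potential risk, examined by "measuring total frequency of high/very high risk discrepancy occurrence and the frequency of high/very high risk discrepancy occurrence per patient".
- **Data analysis.** The sentence that names the primary endpoint describes it by all instances: in total, per patient and per medication group. The next sentence lists four comparisons: all instances and high/very high risk instances, each per group and per patient. No order is given. The same section states: "All tests will be two-tailed, and significance will be set at α = 0.05".
- **Power calculation and sample size determination.** The calculation rests on "a primary endpoint of a 50% reduction in medication discrepancies (3.12 ± 2.5 per patient [6] to 1.56 per patient"), and "41 participants will be required per treatment arm to achieve ≥80% statistical power". This is the count of discrepancies of any risk level. No mean, SD, share or power is given for the high/very high risk count.

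**The concern.** The text under the primary outcome heading and the text that sizes the trial do not measure the same thing. High/very high risk discrepancies are a subset of all discrepancies. A subset of a count has a lower mean and usually a larger spread relative to that mean, so the same percentage reduction is harder to detect.

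Two consequences follow if this is left open.

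- A non-significant result on the high/very high risk count could be read as a negative finding from a trial with at least 80% power, although no power was calculated for that count.
- With two counts, each tested at 0.05, and no statement of which one decides the primary aim, a positive claim could rest on whichever reaches significance. The chance of a false claim would then exceed 5%.

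**Working it through.** **Inputs from the protocol article.** Control mean 3.12, SD 2.5, intervention mean 1.56 and 41 per arm (sample size section); two-sided alpha 0.05 (Data analysis). All figures below take 41 analysed per arm.

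**Step 1: the plan's own figure.** With a common SD,

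n per arm = 2 × (1.960 + 0.842)² × 2.5² / 1.56² = 40.3, rounded up to 41.

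Power at 41 per arm: 1.56 / (2.5 × √(2/41)) = 2.825; 2.825 − 1.960 = 0.865; Φ(0.865) = 80.7%.

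The stated 41 per arm and at least 80% are reproduced, for the all-discrepancy count.

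**Step 2: what is missing for the other count.** The share p of discrepancies rated high or very high is not in the document, so p has to be assumed. Three further assumptions are needed:

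- per-patient counts are negative binomial, matched to 3.12 ± 2.5, so that k = 3.12² / (6.25 − 3.12) = 3.11;
- each discrepancy is high/very high risk with probability p, so the subset has mean 3.12p, the same k, and SD = √(m + m²/k) with m = 3.12p;
- the reduction is 50% at every risk level.

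**Step 3: power for the high/very high risk count at 41 per arm.** The plan's method uses the control-arm SD in both arms: power = Φ( (m/2) / (SD × √(2/41)) − 1.960 ). Worked example at p = 20%: m = 0.624 and SD = √(0.624 + 0.624²/3.11) = 0.866; 0.312 / (0.866 × 0.2209) = 1.63; Φ(−0.33) = 37%. The last column simulates the negative binomial counts and applies a Welch t-test.

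| Assumed share p | Control mean | Control SD | Plan's common-SD method | Negative binomial counts, Welch test |
|---|---|---|---|---|
| 10% | 0.31 | 0.59 | 23% | 28% |
| 20% | 0.62 | 0.87 | 37% | about 48% |
| 30% | 0.94 | 1.10 | 48% | 62% |
| 40% | 1.25 | 1.32 | 57% | 72% |
| 60% | 1.87 | 1.73 | 69% | 84% |
| 100% (all discrepancies) | 3.12 | 2.50 | 81% | about 94% |

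Only the common-SD column is on the same basis as the plan's 80%. The other column starts from about 94% for all discrepancies, because the SD in the intervention arm falls with the mean. It must be read against 94%, not 80%.

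**Step 4: sensitivity.** In the Welch column power is about 15% at a 5% share and passes 80% once the share is a little above one half. If the SD instead shrank in exact proportion to the mean, power would stay at 80.7% at every share.

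**Step 5: false-positive rate if either count could carry the claim.** With no treatment effect, the same counts were simulated for 41 per arm, the high/very high risk subset was drawn from them at share p, and both were tested at two-sided 0.05. At least one was significant in about 9% of trials at shares of 10% and 20%, and in about 8% at shares of 30% and 40%.

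**The case against.** The strongest reply is that the primary endpoint is the all-discrepancy count and the sample size matches it. H1, the sentence in Data analysis that names the primary endpoint, and the sample size section all use discrepancies of any risk, and Table 3 lists the per-patient frequency of discrepancies. Even the Primary outcome section speaks of discrepancies without a risk restriction before it turns to the composite. This much stands: a reader might infer that the protocol defines its primary endpoint as high/very high risk discrepancies only, and the documents do not support that. The reply does not remove the conflict. The primary outcome text gives the high/very high risk counts as the measure of its composite, and the primary aim includes severity.

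A second reply is that no specific power shortfall can be derived. This stands too. A reader might conclude that the trial has, say, 28% to 72% power for its primary endpoint. That range needs an assumed 10% to 40% share, a count model and an equal relative effect at every risk level. The last is not assured, since the intervention is tailored in intensity to the patient.

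A third reply is that no sentence allows success to be declared on either count, and that test ordering is often left to a statistical analysis plan, which is not shown. That is fair: inflation of the false-positive rate is what the open wording permits, not what the protocol plans. Naming the primary measure, however, belongs to the protocol, which here names it in more than one way.

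**Conclusion.** The point holds as an unresolved primary measure that was powered in only one of its forms. The conflict between the sections can be read directly in the text and rests on no assumption. The power of at least 80% is correct for the all-discrepancy count (80.7% at 41 per arm) and is not shown for the high/very high risk count.

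The size of any shortfall is illustrative. On the plan's own method, with the SD derived as in the working and a 50% reduction at every risk level, power for the high/very high risk count would be about 23% to 57% at shares of 10% to 40%, and 69% at 60%. The either-count error of about 8% to 9% likewise depends on the assumed share, and applies only if a claim on either count is allowed. It is safe to say that 41 per arm would probably be too few if such discrepancies are a minority with the same relative reduction. It is not safe to say that the trial is underpowered for its primary endpoint.

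**What to change.** - **Primary outcome:** name the number of discrepancies of any risk level per patient at t3 as the single primary endpoint. This matches H1 and the sample size section.
- **Secondary outcomes:** make the number of high/very high risk discrepancies per patient at t3 the first secondary endpoint, tested only if the primary result is significant. Each test can then be run at two-sided 0.05 without raising the error rate across the two.
- **Study aims and Data analysis:** align the wording with this order. Present the group totals and the breakdown by medication group as descriptive.
- **Sample size section:** state that the power of at least 80% applies to the all-discrepancy count only, and that the high/very high risk count was not powered. Assumed shares need not be written into the protocol.

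The cost is wording in four or five places, with no extra patients. This matters because Trial status reports recruitment as complete. The Primary outcome section places the blinded risk ranking at the completion of the study, so the order can be fixed and dated before the high/very high risk counts exist. The small downside is that no confirmatory claim on high/very high risk discrepancies is possible unless the primary test succeeds.
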